### Sample size calculation

2.5

Sample size calculation is based on the primary outcome of FBG, using G*Power 3.1 software. A 2 × 3 analysis of variance (ANOVA) was selected for sample size calculation due to its suitability for assessing group (Lo-TENS vs. sham) × time (baseline, post-intervention, 4-week follow-up) interactions for continuous primary outcomes; mixed-effects models will be used for secondary analyses to account for potential missing data, consistent with modern pilot trial statistical practices. Based on prior Lo-TENS studies in T2DM (*f* = 0.282, the most conservative effect size) (20), *α* = 0.05, power = 0.80, and a 20% attrition rate, a total sample size of 50 participants (25 per group) is required. This sample size is appropriate for a pilot RCT to estimate effect sizes and assess feasibility.

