### Outcomes

2.4

All outcomes are measured at baseline, post-intervention (week 4), and 4-week follow-up (week 8) (Table 2).

**Table 2 tab2:** Timeline for participants’ enrolment, interventions, and assessments.

Time point	Study period							
	Enrolment	Allocation	Intervention					Close-out (follow-up)
	1 week before	0	1st week	2nd week	3rd week	4th week	Post-intervention	8th week
ENROLMENT								
Eligibility screen	X							
Informed consent	X							
Randomization		X						
INTERVENTIONS:								
Lo-TENS + routine clinical management								
Sham stimulation + routine clinical management								
ASSESSMENTS:								
24-h ABPM	X						X	X
FBG	X						X	X
TC	X						X	X
TG	X						X	X
Plasma glucose	X						X	X
HbA1c	X						X	X
HDL	X						X	X
LDL	X						X	X
LDL-cholesterol	X						X	X
24-h dynamic ECG	X						X	X
CRP	X						X	X
Adiponectin	X						X	X
TNF-α	X						X	X
FGF21	X						X	X
Norepinephrine	X						X	X

ABPM, ambulatory blood pressure monitor (the average, standard deviation, maximum and minimum values of patient’s daytime, nighttime, and all-day systolic, diastolic blood pressure, mean arterial pressure, and pulse pressure); CRP, C-reactive protein; ECG, electrocardiogram; FBG, fasting blood glucose; FGF21, fibroblast growth factor 21; HbA1c, glycosylated hemoglobin; HDL, high-density lipoprotein cholesterol; LDL, low-density lipoprotein; LDL-cholesterol, low-density lipoprotein cholesterol; TC, total cholesterol; TG, triglyceride; TNF-α, tumor necrosis factor-α.

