#### Feasibility outcomes (pilot-specific)

2.4.3

Feasibility outcomes include: (1) Recruitment rate (number of eligible participants recruited per month); (2) Intervention adherence rate (percentage of participants who complete ≥80% of TENS/sham sessions); (3) Attrition rate (percentage of participants who drop out before post-intervention/follow-up); (4) Adverse event rate (number of adverse events related to TENS/sham stimulation) (21).

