### Statistical analysis

2.8

The data analysis will be conducted using the Statistical Package for Social Sciences (SPSS) version 26. To ensure the accuracy of the data entry, it will be performed by two independent researchers who will cross-verify the input data for consistency. The baseline characteristics will be assessed using appropriated statistical tests based on the data distribution: independent *t*-tests for normally distributed data, Mann–Whitney *U* tests for non-parametric data, and Chi-square tests for categorical variables.

If the parameters meet the criteria for normal distribution, a repeated-measures ANOVA will be used to examine group × time interactions for primary and secondary outcomes. To account for multiple comparisons across the three co-primary outcomes (office BP, FBG, LDL-C), a Bonferroni correction will be applied, setting the significance level at *p* < 0.0167. Any two of these outcomes reach significance will be considered positive. Secondary outcomes will be analyzed descriptively and inferentially without correction, given their exploratory nature. To test the mechanistic hypothesis that ANS modulation and inflammatory/metabolic biomarkers mediate Lo-TENS’s effects on primary outcomes, we will conduct bootstrapped mediation analysis (5,000 resamples) using the PROCESS macro for SPSS 26. For each primary outcome (SBP, FBG, LDL-C), we will test whether the effect of Lo-TENS is mediated by pre-specified mechanistic markers (HF-HRV, norepinephrine, IL-6, and adiponectin), with 95% confidence intervals used to determine significant mediation. The magnitude of the effects will be quantified using partial eta-squared (*η_p_*^2^), with thresholds of 0.01, 0.06, and 0.14 indicating small, medium, and large effect sizes, respectively.

Subsequently, all analyses will be reiterated after the exclusion of drop-outs to conduct a per-protocol analysis.

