## Glossary

ANS: Autonomic Nervous System
ABPM: 24-Hour Ambulatory Blood Pressure Monitoring
CRP: C-Reactive Protein
EH: Essential Hypertension
ELISA: Enzyme-Linked Immunosorbent Assay
FBG: Fasting Blood Glucose
FGF21: Fibroblast Growth Factor 21
HF-HRV: High-Frequency Heart Rate Variability
IL-6: Interleukin-6
ITT: Intention-to-Treat
LDL: Low-density lipoprotein
LDL-C: Low-Density Lipoprotein Cholesterol
LF-HRV: Low-Frequency Heart Rate Variability
Lo-TENS: Low-Frequency Transcutaneous Electrical Nerve Stimulation
NE: Norepinephrine
PP: Per-Protocol
RCT: Randomized Controlled Trial
SBP: Systolic Blood Pressure
SF-36: 36-Item Short Form Health Survey
T2DM: Type 2 Diabetes Mellitus

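### The planned repeated-measures ANOVA keeps only participants with all three visits; the mixed model named for missing data should be primary, and sections 2.5 and 2.8 need reconciling

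*Protocol article*

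**What the plan says.** - **Main analysis.** Section 2.8 names "Statistical Package for Social Sciences (SPSS) version 26" as the software. If normality holds, "a repeated-measures ANOVA will be used to examine group × time interactions for primary and secondary outcomes". No other model, imputation or analysis set is given for the main analysis.
- **Visits and timing.** Section 2.4 sets three visits: baseline, week 4 and week 8. The Methods paragraph of the abstract places the co-primaries (office SBP, FBG, LDL-C) at post-intervention, which is week 4.
- **Missing data.** Section 2.5 allows for 20% attrition in a total of 50. In the same paragraph it says that "mixed-effects models will be used for secondary analyses to account for potential missing data". Section 2.8 does not mention this model.
- **Second analysis set.** Section 2.8 ends by saying that "all analyses will be reiterated after the exclusion of drop-outs to conduct a per-protocol analysis". It does not define a drop-out. The nearest definition is the feasibility outcome in section 2.4.3: "Attrition rate (percentage of participants who drop out before post-intervention/follow-up".
- **Intention to treat.** It appears only as a Glossary entry, "ITT: Intention-to-Treat".
- **Adherence.** Table 1 (item 9) and section 2.4.3 both use completion of at least 80% of sessions as the threshold.

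**The concern.** A classical repeated-measures ANOVA needs a complete set of visits for each participant. A person measured at baseline and week 4 but not at week 8 therefore contributes nothing, even to the week-4 comparison that the abstract makes primary. The plan sees the problem and names a model that handles it, but does not give that model the primary role. It then offers a per-protocol repeat that removes people who, on the likely meaning of drop-out, are already gone.

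Two things are at stake. Week-4 data that were collected go unused. The main estimate is also a completers' comparison, with no clearly planned check beside it. A stated purpose of the trial is to supply effect sizes for a definitive trial, so bias from attrition would carry into that trial's sample size. Section 3.4 itself names frailty and limited mobility as likely causes of loss, so loss unrelated to health cannot be taken for granted.

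**Working it through.** **1. Inputs.** From the protocol article: N = 50 (25 per arm), 20% attrition, three visits, and a Bonferroni level of 0.0167. Listwise deletion is the default behaviour of SPSS repeated-measures ANOVA; the article does not state it. Correlations between visits, the timing of losses and their cause are not in the article and are assumed below.

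**2. The plan's own figure.** 50 × (1 − 0.20) = 40 completers. Whether 50 follows from f = 0.282, α = 0.05 and power 0.80 depends on a between-visit correlation that is not stated. A correlation of 0.05 gives 40, and 40/0.8 = 50. A correlation of 0.5 gives 22, and 22/0.8 = 27.5, so 28. The figure can be neither confirmed nor called wrong, and this point does not rest on it.

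**3. Analysis sets at 20% attrition** (drop-out = misses a visit, no imputation, no isolated missing values):

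| Analysis | Participants |
|---|---|
| Repeated-measures ANOVA (section 2.8) | 40 |
| Repeat without drop-outs (section 2.8) | 40 |
| Mixed model using every available visit | up to 50 |

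The first two differ by 40 − 40 = 0.

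**4. Week-4 data discarded.** Of the 10 losses, the number with a valid week-4 value depends on timing: none after week 4 gives 0, half gives 5, all gives 10.

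**5. Precision, illustrated.** For a baseline-adjusted week-4 comparison, noncentrality = δ²N / [4(1 − ρ²)]. Assume δ = 0.8 SD and ρ = 0.5, with α = 0.0167:
- N = 40: 0.64 × 40 / 3 = 8.53, power 66%.
- N = 45: 0.64 × 45 / 3 = 9.60, power 73%.

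This is not the planned group × time test. It shows only what 5 extra participants are worth in a week-4 comparison.

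**6. Bias, illustrated by simulation.** Assumptions: 25 per arm, true week-4 effect 0.50 SD, baseline to week-4 correlation 0.6, all of the stated loss after week 4, and the difference in change from baseline estimated in completers.

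| Loss after week 4 | Completers' estimate |
|---|---|
| 20% per arm, tied to a poor week-4 value in sham only (odds ratio 3 per SD) | 0.42 to 0.43 |
| 10% per arm, same mechanism | 0.46 |
| Same dependence in both arms | 0.48 to 0.50 |
| Random | 0.50 |

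Using all week-4 values returns 0.50 throughout. The 10% row matches the half-after-week-4 case in step 4 (5/50 = 10%).

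**7. Scale.** With 20 completers per arm, the sampling SD of the change difference is √[2(1 − 0.6) × 2/20] = 0.28. The largest bias shown, 0.50 − 0.42 = 0.08, is less than a third of that and runs towards no effect.

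**The case against.** **A mixed-model analysis of the primaries may already be intended.** A reader might infer that the plan yields no intention-to-treat result at all. The article does not support that. Section 2.5 speaks of secondary analyses, not secondary outcomes, and the clause directly follows a reference to the continuous primary outcomes. It can fairly be read as a sensitivity analysis of the co-primaries. The Glossary lists both ITT and PP, which suggests that the first run was meant as intention to treat. What remains is that section 2.8 omits the model and assigns ANOVA to secondary outcomes as well, and that on either reading the main result uses completers only.

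**The two runs need not be identical.** A reader might also infer that the main and per-protocol results must be the same numbers. That too goes beyond the text. Section 2.8 does not define drop-outs. Someone who stops sessions but attends visits could be in the first run and out of the second, and a failed assay could also separate the sets. Imputation may be specified in a document not shown. The supportable statement is that the sets largely coincide under the section 2.4.3 meaning and without imputation.

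**The size is modest and conditional.** This stands. The bias needs outcome-dependent loss that differs between arms. In the case shown it would shrink an effect, not create one.

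**It is a pilot.** This lowers the urgency. It does not remove the point, because effect-size estimation is a stated aim and section 2.8 sets a significance rule for a positive result.

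**Conclusion.** The point holds in this form. The stated primary analysis by default discards participants with any missing visit, including those with valid week-4 co-primary data. The model that the plan itself names for missing data is not primary and is absent from section 2.8. The per-protocol repeat is likely to add little or nothing as a check on attrition. At the plan's 20% attrition, about 40 of 50 are analysed. If half the losses come after week 4, 5 usable week-4 records are lost, and the bias ranges from none to about 0.04 SD at that level of loss. It reaches about 0.08 SD if all the loss is after week 4 and tied to outcome in the sham arm only.

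These conclusions rest on SPSS default deletion, no imputation, and drop-out meaning a missed visit. This should be fixed, but it is not a fatal flaw in a pilot.

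**What to change.** - **Sections 2.5 and 2.8:** make the linear mixed model (visit as a category, group × visit, baseline-adjusted) the primary analysis of the three co-primaries in all randomised participants as allocated, using every available visit. State that the week-4 group contrast is the co-primary test.
- **Section 2.8:** state which model applies to the secondary outcomes, so that the two sections agree. Repeated-measures ANOVA in completers can stay as a supporting analysis.
- **Per-protocol set:** define it by the threshold of at least 80% of sessions in Table 1 and section 2.4.3, instead of by drop-out status.

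The cost is a few sentences. SPSS 26 fits the model, and no new data or visits are needed. The mixed model recovers the discarded week-4 values. It does not remove bias where loss before week 4 depends on values that were never observed, so losses by arm and timing should still be reported alongside the reasons already promised in section 3.4.

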However, no pilot randomized controlled trial (RCT) has yet investigated Lo-TENS for common multimorbidity in older adults, nor explored its mechanistic pathways through ANS and inflammatory/metabolic biomarkers. Low-frequency transcutaneous electrical nerve stimulation (Lo-TENS; ≤10 Hz) is a non-invasive, low-risk intervention that modulates ANS activity by stimulating peripheral nerves (14). Prior studies have shown that Lo-TENS reduces sympathetic tone (measured via plasma norepinephrine levels and HRV) and improves clinical outcomes in patients with single chronic conditions, such as EH and T2DM (15–17) For example, Stein et al. demonstrated that 2 Hz Lo-TENS robustly reduces sympathetic activity and increases parasympathetic tone in healthy adults (15), and subsequent studies have validated these effects in older adults with cardiovascular conditions (18, 19). A recent randomized trial in patients with type 2 diabetes further suggested that TENS may improve glycemic variability, although its effect on HbA1c remains inconclusive, warranting further mechanistic investigation (20).

A pilot RCT is critical for this research question to assess feasibility (e.g., recruitment, intervention adherence, attrition) and estimate effect sizes for a subsequent definitive trial (21). As an pilot RCT, this study first aims to assess the feasibility of Lo-TENS delivery in older adults with multimorbidity and estimate effect sizes for a subsequent definitive trial. Second, we examine the efficacy of Lo-TENS as an adjunct to routine clinical management for improving blood pressure, glycemic control, and lipid profiles in older adults with common multimorbidity (≥2 of EH, T2DM, hyperlipidemia). Third, we explore the underlying mechanisms of Lo-TENS by testing whether changes in ANS function (HRV, norepinephrine) and inflammatory/metabolic biomarkers (IL-6, adiponectin, FGF21) mediate its effects on clinical outcomes (22, 23).

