#### Eligibility criteria

2.2.1

Inclusion criteria: (1) Aged ≥60 years; (2) Diagnosis of multimorbidity, defined as co-occurrence of ≥2 of the following: EH (diagnosed per Chinese Guidelines for the Management of Hypertension (26)), T2DM (diagnosed per American Diabetes Association guidelines (27)), hyperlipidemia (diagnosed per Chinese Guidelines for the Management of Dyslipidemia in Adults (28)); (3) Medically stable, defined as no acute exacerbation of EH, T2DM, or hyperlipidemia in the past 3 months and no hospitalizations for cardiovascular/metabolic events (e.g., myocardial infarction, stroke, diabetic ketoacidosis) in the past 6 months; (4) Able to understand and comply with the intervention protocol (e.g., attend 4 weeks of TENS sessions); (5) Voluntary participation and signed informed consent.

Exclusion criteria: (1) Contraindications to TENS (e.g., pacemaker/implantable cardioverter-defibrillator, skin lesions at electrode sites, pregnancy); (2) Severe cognitive impairment (Mini-Mental State Examination score <24); (3) Severe comorbidities (e.g., end-stage renal disease, malignant tumors); (4) Use of other non-pharmacological interventions for cardiovascular/metabolic conditions (e.g., acupuncture, massage) within the past 1 month; (5) Unstable medication regimens for EH/T2DM/hyperlipidemia (e.g., dose changes within the past 2 months).

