### Randomization and allocation concealment

2.6

Randomization sequence is generated using the Random Allocation Software (version 2.0), a validated online tool. Participants are allocated to groups in a 1:1 ratio using permuted blocks of size 4 (to ensure balanced group sizes). Allocation concealment is achieved using opaque, sealed envelopes labeled with sequential participant numbers; envelopes are opened by a researcher not involved in participant recruitment or outcome assessment after informed consent is obtained.

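### The FBG effect size comes from T2DM studies, but eligibility does not require T2DM; each co-primary can be diluted by participants without the matching condition, and neither allocation nor analysis allows for it

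*Protocol article*

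**What the plan says.** All places are in the protocol article.

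- **Sample size (2.5).** "Sample size calculation is based on the primary outcome of FBG, using G*Power 3.1 software". The effect size, f = 0.282, is described as "Based on prior Lo-TENS studies in T2DM" and is called the most conservative one. With α = 0.05, the section gives "power = 0.80, and a 20% attrition rate, a total sample size of 50 participants (25 per group) is required".
- **Source population (Introduction).** The study cited for that effect size is introduced as "A recent randomized trial in patients with type 2 diabetes further suggested that TENS may improve glycemic variability".
- **Eligibility (2.2.1).** "Diagnosis of multimorbidity, defined as co-occurrence of ≥2 of the following": hypertension, T2DM, hyperlipidemia. Hypertension plus hyperlipidemia without diabetes qualifies, as do the other two pairs. No minimum SBP, FBG or LDL-C is listed.
- **Allocation (2.6).** "Participants are allocated to groups in a 1:1 ratio using permuted blocks of size 4". No stratification factor is named.
- **Analysis (2.8).** Each co-primary is tested by a repeated-measures ANOVA for group × time, at 0.0167. Two of three significant results count as a positive trial. No condition term, baseline covariate or condition-restricted analysis is described. Section 3.5 mentions subgroup analyses only as future work.

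**The concern.** The effect size comes from patients who all had diabetes and is applied to a sample whose diabetes share is neither fixed nor stated. If Lo-TENS lowers FBG mainly where FBG is raised, participants without T2DM pull the average effect down, and the 80% in 2.5 does not describe the trial that will be run. The same can happen to SBP through participants without hypertension, and to LDL-C through participants without hyperlipidemia.

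Two things are at stake. One is the stated power, and with it the two-of-three success rule. The other is the effect size passed to the definitive trial, which the Introduction makes part of the first aim. An average over an unplanned case mix is hard to carry into a trial whose mix may differ.

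**Working it through.** **Inputs from the protocol article.** f = 0.282, α = 0.05, power 0.80, 20% attrition, N = 50 (2.5); 2 groups × 3 time points (2.5); test level 0.0167 (2.8). Completers: 50 × 0.8 = 40.

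**Inputs not given.** The T2DM share p, the within-person correlation ρ, the sphericity factor ε, and the FBG effect in participants without T2DM.

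**Step 1: the plan's own figure.** For the group × time interaction with k = 2 groups, m = 3 times and ε = 1:

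λ = f² · N · m / (1 − ρ), df1 = (k − 1)(m − 1) = 2, df2 = (N − k)(m − 1)

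With ρ = 0.5 and ε = 1 this needs 22 completers, or 28 enrolled after attrition, not 50. A total within 2 of 50 appears only with settings the article does not state, such as ρ = 0.1 and ε = 1 (38 completers, 48 enrolled). This does not prove 50 wrong, but a baseline has to be chosen. I took the plan at its word and solved for the ρ that gives 80% power at 40 completers:

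- ρ ≈ 0.048, df2 = 38 × 2 = 76
- λ = 0.282² × 40 × 3 / (1 − 0.048) ≈ 10.02

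**Step 2: dilution.** Assume no FBG effect without T2DM. The mean effect is then p times the effect in diabetes. How far f falls depends on the SD of change:

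- SD unchanged: f becomes p · f, so λ becomes p² · 10.02.
- Participants without T2DM add no change variance: f becomes √p · f, so λ becomes p · 10.02.

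Power at 40 completers, α = 0.05:

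| T2DM share p | f, SD unchanged | Power | f, no added variance | Power |
|---|---|---|---|---|
| 1 | 0.282 | 80% | 0.282 | 80% |
| 0.75 | 0.212 | 54% | 0.244 | 67% |
| 2/3 | 0.188 | 44% | 0.230 | 62% |
| 0.5 | 0.141 | 26% | 0.199 | 49% |

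**Step 3: sensitivity to the calibration.** With ρ = 0.5 and ε = 1, the same 40 completers have 98% power undiluted, 83–92% at p = 0.75, 73–89% at p = 2/3 and 47–78% at p = 0.5. The loss is still there but starts from a higher level.

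**Step 4: how far all three co-primaries can be affected.** Two conditions are required, so each participant lacks at most one of the three. The shares lacking hypertension, T2DM and hyperlipidemia therefore sum to at most 100%, and they sum to zero if everyone has all three.

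**Step 5: chance imbalance.** Blocks of 4 balance arm size, not condition. Treating the T2DM counts as two independent Binomial(25, 2/3) variables, the chance of a difference of 5 or more is 17.6%.

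**The case against.** - **A mixed sample is intended.** The Introduction argues for one sympathetic mechanism behind all three conditions, so multimorbid patients are the target and the all-participant effect is legitimate. This stands, and that estimate should stay primary. It does not supply an effect size for the mixed sample.
- **Dilution is possible, not established.** A reader might infer that each co-primary *is* diluted. The documents give no case mix; if everyone had all three conditions there would be no dilution. A zero effect without diabetes is likewise an assumption.
- **The lowest power figures are one bound.** They need an unchanged SD and a correlation near 0.05. Step 3 shows how much depends on the latter.
- **The 0.0167 level.** A reader might quote power at that level as the cost of case mix. The calibrated design has only 65% there with no dilution at all, so part of any such shortfall comes from the separate mismatch between α in 2.5 and in 2.8.
- **Imbalance.** Stable differences in FBG level largely cancel in a group × time test. Imbalance matters only if change over time differs by diabetes status, which the documents do not show. The 17.6% supports stratifying but does not demonstrate bias.
- **The cited diabetes trial.** The Introduction says that "TENS may improve glycemic variability, although its effect on HbA1c remains inconclusive". A reader might infer that the source holds no FBG effect. One sentence about a study not at hand cannot show that. Nor do the documents show that FBG will be skewed or two-peaked.
- **It is a pilot.** True, and it limits the consequences. But 2.5 still claims 80% power, 2.8 sets a success rule, and effect-size estimation is a stated aim.

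**Conclusion.** The point holds as a mismatch within the protocol article: the effect size is specific to T2DM, eligibility is not, and neither allocation nor the stated model takes account of who has which condition. The 80% in 2.5 applies only if nearly all participants have T2DM, or if the FBG effect is the same without it, and the article states neither.

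For T2DM shares from 75% down to one half, power at α = 0.05 would lie between 67% and 26%. That range rests on three assumptions: no FBG effect without T2DM, the design calibrated to its own 80% at 40 completers, and an SD of change between the two bounds. A partial effect or a higher within-person correlation narrows the loss. The documents do not support saying that dilution will occur or how large it will be. They support saying that it can occur, and that the plan neither sizes it nor prepares for it. This should be changed, but it does not invalidate the pilot.

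**What to change.** 1. **Section 2.5.** State the expected T2DM share, scale f by it (showing both SD assumptions) and restate the power for 50 participants. Enrolment stays at 50.
2. **Section 2.6.** Stratify by T2DM status for participants still to be enrolled. One factor is enough at this size; the other two conditions are handled in the model.
3. **Section 2.8.** Analyse each co-primary with a baseline-adjusted model: post-intervention value as outcome and baseline value as covariate, for example ANCOVA or a mixed model. Include status for the matching condition: hypertension for SBP, T2DM for FBG, hyperlipidemia for LDL-C. Baseline is one of the three repeated levels in the present ANOVA, so this changes the form of the model.
4. **Section 2.8.** Keep the all-participant estimate as primary. Beside it, pre-specify each co-primary's estimate with confidence interval in participants with the matching condition. Report both, with the case mix, for planning the definitive trial.

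**Cost.** Two allocation lists instead of one, a changed model, a less favourable stated power, and three less precise subset estimates. At a two-thirds share, for example, the FBG subset has about 40 × 2/3 ≈ 27 completers. Items 1, 3 and 4 can be settled at any time before unblinding; item 2 loses value as allocation proceeds.

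### The stated 80% power is for FBG alone at alpha 0.05; it is not the power of the planned test at p < 0.0167 or of the two-of-three success rule

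*Protocol article*

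**What the plan says.** Section 2.5 (Sample size calculation) opens with "Sample size calculation is based on the primary outcome of FBG, using G*Power 3.1 software". The model is the group × time interaction: "A 2 × 3 analysis of variance (ANOVA) was selected for sample size calculation". The effect size f is given as "0.282, the most conservative effect size", taken from earlier Lo-TENS studies in type 2 diabetes (T2DM), with alpha 0.05. The conclusion is "power = 0.80, and a 20% attrition rate, a total sample size of 50 participants (25 per group) is required". The section ends by calling this size suitable for a pilot that estimates effect sizes and assesses feasibility.

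Section 2.8 (Statistical analysis) sets a different standard. For the three co-primary outcomes (office blood pressure, FBG, LDL-C), "a Bonferroni correction will be applied, setting the significance level at" p < 0.0167. It then adds "Any two of these outcomes reach significance will be considered positive".

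The article gives no effect size for SBP or LDL-C, no correlation among the repeated measures or among the outcomes, and no power at 0.0167 or for the two-of-three rule.

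**The concern.** A power figure describes one test at one significance level. Here the level in the calculation (0.05) is three times the level in the analysis (0.0167). The calculation concerns one outcome, while success needs two of three. A reader of section 2.5 would suppose that the trial has an 80% chance of meeting its success criterion under the assumed effect, and nothing in the article supports that.

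This matters when the result is read. A non-significant outcome could be taken as a negative from an 80%-powered test, although no such power was calculated for the test applied. The figure could also be carried into planning of the definitive trial.

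**Working it through.** **Inputs.** From section 2.5: f = 0.282, alpha 0.05, power 0.80, 2 groups, 3 time points, 20% attrition, N = 50, so 50 × 0.8 = 40 completers. From section 2.8: alpha 0.05/3 = 0.0167 per outcome, with success defined as at least two of three. Not stated, so varied here: the correlation ρ among repeated measures. Sphericity is assumed.

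**Formula** (G*Power default convention, within-between interaction): noncentral F with λ = f² × N × 3 / (1 − ρ) and df = 2 and 2(N − 2).

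**Step 1: the plan's own figure.** Smallest even N for 80% at alpha 0.05, then divided by 0.8 for attrition:

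| ρ | completers | enrolled |
|---|---|---|
| 0 | 42 | 53 |
| 0.05 | 40 | 50 |
| 0.1 | 38 | 48 |
| 0.3 | 30 | 38 |
| 0.5 | 22 | 28 |

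So 50 is reproduced exactly at ρ of about 0.05.

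**Step 2: same design, planned alpha.** Take section 2.5 at its word: 40 completers give 80% at 0.05. With df 2 and 76 the critical F is 3.12, and 80% power needs λ = 10.02. Check: 0.282² × 40 × 3 = 9.54, and 9.54 / (1 − 0.048) = 10.02. At 0.0167 the critical F rises to 4.32. The same λ then gives power of 65%.

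**Step 3: the two-of-three rule.** Let p = 0.652 and a = 0.0167, with independent outcomes.
- All three respond equally: 3p²(1 − p) + p³ = 0.72. By simulation, if the outcomes correlate at 0.5 to 0.8, this becomes about 0.66 to 0.68.
- Two respond: p² + 2p(1 − p)a = 0.43.
- Only FBG responds: 2pa(1 − a) + a² = 0.02.

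At the same implied correlation, 80% for FBG at 0.0167 would need 54 completers (68 enrolled). For two of three with equal independent effects it would need 46 (58 enrolled).

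**Step 4: dependence on ρ.** 40 completers, alpha 0.0167:

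| ρ | FBG | two of three, equal independent effects |
|---|---|---|
| 0.05 | 65% | 72% |
| 0.15 | 71% | 80% |
| 0.28 | 80% | 90% |
| 0.5 | 94% | 99% |

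At ρ = 0.5 the rule has 88% power if two outcomes respond and 3% if only FBG does.

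**Step 5: can both statements hold?** FBG power at 0.0167 reaches 80% only when ρ is at least about 0.28. At ρ = 0.28, 80% at alpha 0.05 needs only 32 completers, or 40 enrolled. Under this convention, no value of ρ makes 50 the number required for 80% at 0.05 and also gives 80% for FBG at 0.0167.

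**The case against.** The strongest reply is that power may be ample. Repeated FBG values in medically stable participants on fixed regimens could well correlate above 0.28, and then 40 completers exceed 80% at 0.0167. Larger effects on SBP and LDL-C would also help: with 90% power for each of those and 65% for FBG, two-of-three power is 93%. This stands, and it rules out saying flatly that the trial is underpowered. It does not rescue section 2.5, because the same correlations mean that fewer than 50 participants are required.

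The second reply is that this is a pilot. Section 2.5 itself gives a feasibility and effect-size rationale, section 3.4 accepts the limits of the sample, and sections 3.1 and 3.5 leave confirmation to a fully powered trial. This lowers the weight of the point. It does not remove it, since the article still states a power and an efficacy success rule that do not match.

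A reader might infer three stronger charges that the document does not support:
- **That N = 50 is an arithmetic error.** It is reproduced at ρ of about 0.05. Another convention for f gives about 66 completers. Without the correlation and convention, the figure cannot be verified, but it is not refuted.
- **That f is not the most conservative value.** The phrase can mean the smallest of the earlier estimates, and only the cited study could settle that.
- **That power is diluted by participants without T2DM.** Eligibility, "defined as co-occurrence of ≥2 of the following" (hypertension, T2DM, hyperlipidemia), does admit them, while f comes from T2DM studies. The expected share and their FBG response are not given, so this is a caveat and not a measured loss.

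The 2% figure is also no defect in itself: a two-of-three rule is meant to fail when one outcome responds. It shows only that sizing on FBG says little about the chance of success.

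**Conclusion.** The point holds as a mismatch. The 80% in section 2.5 was calculated for one outcome at alpha 0.05 and is not the power of the test or the success rule in section 2.8.

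If section 2.5 is exactly right about its own test, FBG power at the planned threshold is about 65%. Two-of-three power is then about 72%, 43% or 2% as three, two or one outcomes respond. Those figures assume G*Power's default convention, sphericity, 40 completers, equal effects where outcomes respond, and independent outcomes. If the true correlation is higher, power at 0.0167 may exceed 80%, but then 50 is not the number required. Whether there is a shortfall, and how large, cannot be settled from the document.

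**What to change.** Keep N = 50 and revise section 2.5 in one of two ways.

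1. **Keep a power statement.** Give the repeated-measures correlation and the effect-size convention used. State power at 0.0167 for each co-primary outcome and for the two-of-three rule, under stated effects for SBP, FBG and LDL-C and a stated correlation among the outcomes.
2. **Drop it.** Delete the 80% power and the wording that 50 is required, and rest N = 50 on the feasibility and effect-size rationale already in the section, with emphasis on the precision of the estimates.

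In either case, add a sentence saying that f came from T2DM studies while eligibility admits participants without T2DM.

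The cost is a re-run of the calculation and a few sentences, with no extra participants. The downside is that the stated power may become less favourable.
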